## METHODS

The present study is part of a larger research initiative. Findings on the associations between PD and PD subtypes and pulmonary function test (PFT) measures, thoracic ultrasound, diaphragmatic ultrasound, and additional biomarkers will be reported in separate publications. A separate study will examine PD diagnoses and selected outcomes, including thoracic and diaphragmatic ultrasound, in newly diagnosed systemic lupus erythematosus (SLE) patients. Patients were identified through a systematic search of hospital records across all institutions in the Southern Denmark Region. The search includes visits between July 1, 2021, and June 30, 2023, coded as related to SLE or SLE-associated diseases. Participants were enrolled between August 1, 2023, and October 31, 2024. Statistical analyses will commence upon finalization and approval of this SAP.

At a single visit day all tests were performed. All participants start with an outpatient visit, where the primary investigator review the participants' medical history, note the patients' disease activity and damage. Hereafter the participants undergo pulmonary function testing, HRCT scan, and blood and urine samples. Questionnaires are filled out before the visit. The HRCT scans are described after the visits, and finally the participants are diagnosed, at a multidisciplinary discussion (MDD). The study will be reported in accordance with the STROBE guideline (Strengthening of Reporting Observational Studies in Epidemiology). It is not always possible to measure a precise saturation in a six-minute walk test, why we have scored them as good, medium, poor, too bad to use. Good is tests without any outages. Medium is tests with outages, that which we do not suspect affect the measurement. Poor is tests where we suspect, that the outages affect the results. We will only use tests that score good or medium, and the rests will be regarded as missing values.

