## **Logistical regression: Searching for risk factors that are associated with presence of different forms of PD**

Mock-up Table 4. We aim to explore whether one or more clinical measures collected at baseline are associated with the presence of PD. The dependent variable will be the presence or absence of a PD condition of interest (i.e.,  $Y=1$  if yes, otherwise  $Y=0$ ). Logistic regression is the best approach for identifying predictors when the outcome variable is binary (i.e., presence vs. absence of PD) and the goal is to estimate the association between predictor variables and the probability of the outcome while enabling adjustments for potential confounders. Independent variables, as listed in Table 4 and appendix 3, will be analysed in univariate logistic regression to identify potential associations with clinically significant PD conditions. Odds ratios (ORs) with 95% CIs will be used to quantify the strength of associations, with 95% CIs excluding 1 considered indicative of potential significance. In multiple logistic regression analyses we plan to investigate associations that were significant by univariate analyses, however, only a subset of independent variables will be expected to remain statistically significant and independently associated with PD conditions.

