| dsDNA positive ever, no. (%)                           |                                          |                                              |                                               |                                           |                                           |
| SLEDAI 2K, score 0-105                                 |                                          |                                              |                                               |                                           |                                           |
| SLEDAI 2K, without PD, score 0-103                     |                                          |                                              |                                               |                                           |                                           |
| SLICC DI, score 0- 48                                  |                                          |                                              |                                               |                                           |                                           |
| SLICC DI, without PD, score 0-43                       |                                          |                                              |                                               |                                           |                                           |
| Dry cough, composite                                   |                                          |                                              |                                               |                                           |                                           |
| Dry cough, status:                              |                                          |                                              |                                               |                                           |                                           |
| Never, no. (%)                                         |                                          |                                              |                                               |                                           |                                           |

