| BioDMARDs ever, no. (%)                                    |                              |                                  |                                   |                               |                               |
| BioDMARDs current, no. (%)                                 |                              |                                  |                                   |                               |                               |
| Classification criteria EULAR/ACR
criteria, score 0-51, |                              |                                  |                                   |                               |                               |
| Constitutional*, score 0-2                                 |                              |                                  |                                   |                               |                               |
| Haematological*, score 0-4                                 |                              |                                  |                                   |                               |                               |
| Neuropsychiatric*, score 0-5                               |                              |                                  |                                   |                               |                               |
| Mucocutaneous*, score 0-6                                  |                              |                                  |                                   |                               |                               |
| Serosal*, score 0-6                                        |                              |                                  |                                   |                               |                               |
| Musculoskeletal*, score 0-6                                |                              |                                  |                                   |                               |                               |
| Renal*, score 0-4                                          |                              |                                  |                                   |                               |                               |

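### The risk-factor regressions set no bar on variables that overlap with the diagnosis: the full SLEDAI-2K and SLICC DI, a desaturation cut-off that depends on COPD or emphysema, and lung-function tests done before the MDD

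*SAP*

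**What the plan says.** The regression section of the SAP is headed with the aim "Searching for risk factors that are associated with presence of different forms of PD". It enters every row of Table 4 and Appendix 3: "Independent variables, as listed in Table 4 and appendix 3, will be analysed in univariate logistic regression". It then continues: "In multiple logistic regression analyses we plan to investigate associations that were significant by univariate analyses". No variable is barred from that second step.

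The footnotes to Table 4 and Appendix 3 define PD, airway disease, pleural disease, ILD and shrinking lung syndrome (SLS) by the MDD. METHODS gives the order of events. After the clinical review, "Hereafter the participants undergo pulmonary function testing, HRCT scan, and blood and urine samples"; the HRCT scans are described later, "and finally the participants are diagnosed, at a multidisciplinary discussion (MDD"). The SAP does not list what the MDD reviewed and states no blinding to lung function.

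The SAP shows awareness of overlap in two places, both in Table 4. Pleuritis and pleural effusion carry a slash in the PD and Pleural columns. SLEDAI-2K and SLICC DI each have a version without PD. The full scores stay beside these, for example "SLICC DI, score 0- 48", with all cells open, and both recur in Appendix 3. Appendix 3 also leaves open the row "Serosal*, score 0-6" and all the lung-function and walk-test rows. Its footnote changes the 93% desaturation cut-off to 88% for patients with COPD or emphysema.

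**The concern.** A variable that helped to make a diagnosis, or that contains part of it, will be associated with that diagnosis even if it tells us nothing about who develops the disease. Under a risk-factor heading, such an odds ratio invites the wrong reading. Screening on univariate significance can then favour these variables for the multiple models, where they may distort the adjusted estimates for antecedents such as age and smoking. The objective at stake is the last secondary one in Objectives: associations of baseline characteristics and outcome measures with PD and its subtypes.

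**Working it through.** The SAP gives no sample size, prevalence, score distribution or odds ratio for these analyses, so there is no figure of its own to reproduce. The counts and score differences below come from its tables. The odds ratios rest on stated assumptions and show what the overlap alone would produce when there is no true association.

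**1. Rows.** Appendix 3 has 8 plethysmography, 4 diffusion and 4 walk-test rows: 8 + 4 + 4 = 16. The appendix has 42 rows in all. Two of them (full SLEDAI-2K and full SLICC DI) repeat Table 4, so the 16 are among 40 new rows. With five outcomes that is 16 × 5 = 80 univariate odds ratios. Without SLS, which Deviations from SAP removes, it is 16 × 4 = 64.

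**2. PD content of the scores, from the ranges in Table 4.**
- SLEDAI-2K: 105 − 103 = 2 points.
- SLICC DI: 48 − 43 = 5 points.

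**3. Size for the scores.** Scores were simulated for 200,000 patients with no link to PD. PD points were then added for some PD patients and a logistic model was fitted, at PD prevalences of 30%, 50% and 70%.
- SLEDAI-2K (assumed mean 3, SD 2 or 4; 5% or 20% of PD patients score the 2 points): odds ratio 1.01 to 1.10 per point. Without the PD points: 0.995 to 1.002.
- SLICC DI (assumed mean 1.3, SD about 1.6; 10% or 30% of PD patients have one pulmonary point): 1.04 to 1.12 per point. Without the PD points: 0.997 to 1.001.

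**4. Desaturation row.** COPD and emphysema are airway subgroups in Table 3, so the 88% cut-off applies only to patients who have PD. Assume that walk-test saturation has the same normal distribution in everyone (mean m, SD 3) and that a share c of PD patients has COPD or emphysema. Then:
- p0 = Φ((93 − m)/3) without PD, and p88 = Φ((88 − m)/3)
- p1 = c·p88 + (1 − c)·p0 with PD
- OR = [p1/(1 − p1)] / [p0/(1 − p0)]

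| m | p0 | p88 | c | p1 | OR |
|---|---|---|---|---|---|
| 93 | 0.500 | 0.048 | 0.10 | 0.455 | 0.83 |
| 93 | 0.500 | 0.048 | 0.40 | 0.319 | 0.47 |
| 94 | 0.369 | 0.023 | 0.10 | 0.335 | 0.86 |
| 94 | 0.369 | 0.023 | 0.40 | 0.231 | 0.51 |

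The coding alone pulls the odds ratio below 1. If patients with COPD or emphysema truly desaturate more, the two effects oppose each other and the net value is hard to interpret.

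**5. Low FEV1/FVC, as an example of a test the MDD may have used.** Let b be the chance of PD from other causes, and q the chance that a low ratio by itself leads to a PD diagnosis. Then P(PD | low) = 1 − (1 − b)(1 − q) and P(PD | not low) = b.
- q = 0.25, b = 0.5: P = 0.625, odds 1.67 against 1.00, OR 1.67.
- q = 0.50, b = 0.5: OR 3.00. With b = 0.3: OR 4.33.
- q = 0.75, b = 0.3: P = 0.825, odds 4.71 against 0.43, OR 11.0.
- q = 0 (the MDD made no use of the ratio): OR 1.00.

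The range is about 1.7 to 11, and it depends entirely on q, which the SAP does not let us determine.

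**6. Scope.** METHODS opens by assigning "Findings on the associations between PD and PD subtypes and pulmonary function test (PFT) measures" to separate publications. Objectives, Table 2, Appendix 1 and Appendix 3 report those same associations in this study.

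**The case against.** The strongest reply is that the SAP never says the MDD used lung function. It gives only the order of events, and what the MDD saw may be set out in a protocol that is not shown. This stands in part. Use of at least some tests is a strong inference, since no blinding is stated, but it remains an inference. It does not reach the desaturation row or the two full scores, whose overlap can be read from the SAP's own footnotes and ranges. For the scores that overlap is shared content; nothing says the MDD used them.

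The work is also exploratory. The section speaks of exploring potential associations, the lung-function odds ratios sit in an appendix, and readers will see the full and without-PD scores side by side. This lowers the severity, and relabelling would largely cure the univariate tables. It does not help the multiple models, where nothing says which score version enters or whether diagnostic measures may.

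Deviations from SAP has since settled some of this. SLS is dropped, and so are the EULAR/ACR domain rows, including the serosal one, whose overlap was in any case only inferred from the blocked pleural rows. But the domain rows went for readability, and SLICC DI left Appendix 3 only because it is in the main table. No entry takes the lung-function rows out of the regressions.

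A reader might go further and infer that these variables will give the largest associations or will displace smoking and age. The documents do not support that: the calculated effect on the scores is small, desaturation may go the other way, and no multiple model was examined. Striking the whole EULAR/ACR total because of its 6-point serosal domain would be a preference, not a correction.

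**Conclusion.** The point holds in this bounded form and should be fixed. The SAP recognises overlap between predictor and outcome but applies its rule only in part, and sets no bar at the multiple-model step.

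- The full scores are demonstrably contaminated, but the bias is probably small (about 1.01 to 1.12 per point under the assumptions above).
- The desaturation row is circular on its face for PD and airway disease, and its odds ratio may be biased, possibly below 1 (0.47 to 0.86 if saturation is unrelated to disease).
- The 16 lung-function and walk-test odds ratios may be partly true by construction. For low FEV1/FVC the size could be 1.7 to 11, or nil if the MDD did not use the ratio. No figure was derived for TLC, DLCO, KCO or walk distance.

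A reader might infer that the study's main result is compromised. It is not: the primary objective is prevalence, which does not depend on these regressions.

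**What to change.** - Use only the without-PD versions of SLEDAI-2K and SLICC DI as independent variables for PD and its subtypes.
- In any regression, code desaturation with one cut-off that does not depend on diagnosis, or drop that row from the regressions.
- Keep lung-function and walk-test results descriptive in Table 2 and Appendix 1, or label their odds ratios as diagnostic correlates, not risk factors. State what the MDD had before it.
- Bar all these variables from the multiple models for the outcomes they help define. This follows the outcome-by-outcome logic of the slashes in Table 4.
- Reconcile the separate-publications statement in METHODS with Objectives, Table 2 and Appendices 1 and 3.

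No new data are needed. The cost is that a few odds ratios are no longer reported and any multiple model that included these variables is refitted. Because Deviations from SAP shows that analyses have already been run, the changes should be recorded there with this reason.

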### **Comparing the SLE population: Analysis methods comparing PD exposed with PD-unexposed**

Mock-up Table 2. We will compare baseline characteristics across SLE strata, including Systemic Lupus Erythematosus activity and damage scores, patient-reported outcome measures, and pulmonary function tests, for all patients and by the presence or absence of thoracic disease. All 95% confidence intervals (95%CI) will be two sided. The analyses of the secondary outcomes will be performed in sequence. The 95%CI will not be adjusted for multiplicity and should not be used in place of hypothesis testing.

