We plan to present results of PFT test of subtypes of PD (Airway disease, Pleural Disease, ILD, and SLS) and the contrast between groups with means, SD, and a 95% confidence interval for continues data or number and percentages for categorical data in appendixes, see Appendix 1 a-d.

We plan to present the prevalence of High-Resolution CT findings among the investigated study population is presented in an appendix, see appendix 2.

We plan to present results of the univariate logistic analyses, with Odds Ratio and corresponding 95%CI, of the association between selected baseline characteristics and the presence of PD, airway disease, pleural disease, ILD, and SLS in a table, see table 4.

**Table 4.** Impact of selected baseline characteristics and patient related outcome measures in groups of thoracic diseases investigated by univariate logistic regression analyses.

| PD Outcome
vs.
Baseline characteristics | PD
Odds
Ratio
(95%CI) | Airway
Odds
Ratio
(95%CI) | Pleural
Odds
Ratio
(95%CI) | ILD
Odds
Ratio
(95%CI) | SLS
Odds
Ratio
(95%CI) |
|--------------------------------------------------------|------------------------------------------|----------------------------------------------|-----------------------------------------------|-------------------------------------------|-------------------------------------------|
| Age, years                                             |                                          |                                              |                                               |                                           |                                           |
| Female sex, no (%)                                     |                                          |                                              |                                               |                                           |                                           |
| Disease duration, years                                |                                          |                                              |                                               |                                           |                                           |

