| Rheumatoid Arthritis, no. (%)                          |                                          |                                              |                                               |                                           |                                           |
| Systemic Sclerosis, no. (%)                            |                                          |                                              |                                               |                                           |                                           |
| Mixed Connective Tissue Disease, no. (%)               |                                          |                                              |                                               |                                           |                                           |
| Antiphospholipid Syndrome, no. (%)                     |                                          |                                              |                                               |                                           |                                           |
| Pleuritis, positive, no. (%)                           | /                                        |                                              | /                                             |                                           |                                           |
| Pleural effusion, no. (%)                              | /                                        |                                              | /                                             |                                           |                                           |
| Positive APL ever, no. (%)                             |                                          |                                              |                                               |                                           |                                           |
| Decreased complement ever, no. (%)                     |                                          |                                              |                                               |                                           |                                           |

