## Deviations from SAP

In general:

Removed SLS from analysis, because only one was diagnosed with SLS why analyses were of limited value.

Some values have been changed in tables, to make them easier to understand.

Secondary objectives. Describe baseline characteristics has been removed, as it we did not find it was a relevant objective, but it is reported. Further, we have tried make the wording more concise to make them more readable.

Post hoc we developed Figure 2, Appendix 5, and fitted analyses. We included them, as they provided with important information.

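### The univariate logistic screen has no rule for zero cells: with Wald limits, a binary covariate whose exposed patients all have the outcome cannot enter the multiple model

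*SAP*

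**What the plan says.** The SAP's logistic regression section states that "Logistic regression is the best approach for identifying predictors when the outcome variable is binary". The variables listed in Table 4 and Appendix 3 "will be analysed in univariate logistic regression to identify potential associations with clinically significant PD conditions". Odds ratios are read "with 95% CIs excluding 1 considered indicative of potential significance". The next step depends on that reading: "In multiple logistic regression analyses we plan to investigate associations that were significant by univariate analyses".

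The Results section lists the outcomes as "the presence of PD, airway disease, pleural disease, ILD, and SLS in a table, see table 4". The section comparing patients with and without PD adds that "All 95% confidence intervals (95%CI) will be two sided".

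Table 4 has separate rows for individual overlap diagnoses, among them systemic sclerosis, mixed connective tissue disease and rheumatoid arthritis, and also a composite overlap row. The software section names the package and version only. The SAP gives no interval type, no minimum event or exposure count, no exact or penalised method, and no rule for a zero cell.

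The deviations section reports: "Removed SLS from analysis, because only one was diagnosed with SLS why analyses were of limited value".

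**The concern.** In a two-by-two table of a binary covariate against a PD outcome, suppose all of the exposed patients, or none of them, have the outcome. The maximum-likelihood odds ratio is then infinite or zero, and its Wald interval is unbounded for practical purposes. Such an interval cannot exclude 1 whatever the evidence.

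The screen therefore does not behave monotonically. When the last exposed non-case becomes a case, the evidence gets stronger, but the row goes from passing to failing. A covariate that fails is not carried into the multiple model. Evaluating associations with PD and selected subtypes is a stated secondary objective, so a covariate lost this way is lost to that objective. In the opposite direction, with no exposed cases, the row has no reportable odds ratio, although the data do bound it from above.

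**Working it through.** **Inputs.** From the SAP: two-sided 95% intervals, the rule that the interval must exclude 1, and ILD prevalence of about 6% in register studies and 11–37% in clinical studies (Introduction). Assumed, because the SAP gives no figure: 200 patients; 3, 5 or 8 exposed; risk in the exposed equal to that in the unexposed, or 50%, 80% or 90%. There is no planned figure to reproduce.

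**Methods compared.** Let a and b be exposed cases and non-cases, and c and d unexposed cases and non-cases.
- Wald: log OR = ln(ad/bc), SE = √(1/a + 1/b + 1/c + 1/d). The rule fires if |log OR|/SE > 1.96. A zero cell counts as not firing.
- Firth: for one binary covariate the penalty adds ½ to each cell, so OR = (a+½)(d+½)/[(b+½)(c+½)]. The rule fires if twice the drop in penalised log-likelihood at OR = 1 exceeds 3.84, which is the same as the profile interval excluding 1.
- Fisher's exact test, p < 0.05.

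**Step 1: the reversal (200 patients, 22 cases, 6 exposed).**
- 5 of 6 exposed are cases: OR = (5×177)/(1×17) = 52. SE = √(1/5 + 1 + 1/17 + 1/177) = 1.12. The interval is exp(3.95 ± 2.20), about 5.7 to 471. The rule fires (Wald p = 0.0004).
- 6 of 6 exposed are cases: the fitted log OR is about 24 with SE about 11,900, p = 0.998. The rule does not fire, although Fisher p = 0.0000009. Firth gives OR 141, profile interval 15.5 to about 18,600.

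**Step 2: how often the rule fires.** I enumerated all tables, weighting each by its two binomial probabilities.

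| Risk, unexposed | Exposed (n) | Risk, exposed | Wald | Firth | Fisher |
|---|---|---|---|---|---|
| 11% | 5 | 11% (no association) | 0.033 | 0.040 | 0.014 |
| 11% | 5 | 50% | 0.548 | 0.605 | 0.508 |
| 11% | 5 | 80% | 0.627 | 0.959 | 0.943 |
| 11% | 5 | 90% | 0.403 | 0.994 | 0.992 |
| 11% | 3 | 80% | 0.368 | 0.895 | 0.823 |
| 11% | 8 | 80% | 0.828 | 0.996 | 0.993 |
| 6% | 5 | 80% | 0.664 | 0.993 | 0.979 |
| 37% | 5 | 37% (no association) | 0.002 | 0.026 | 0.016 |
| 37% | 5 | 80% | 0.012 | 0.449 | 0.394 |

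Zero cells explain the Wald shortfall. At 80% risk, all 5 exposed are cases with probability 0.8⁵ = 0.328, so Wald cannot exceed 0.672. At 90% the corresponding figures are 0.9⁵ = 0.590 and 0.410.

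At 37% unexposed risk, 4 of 5 exposed cases is also too weak. With 72 of 195 unexposed cases, OR = (4×123)/(1×72) = 6.8 and ln(6.8)/1.13 = 1.70, below 1.96. Only 5 of 5 would be convincing there, and Wald cannot use it.

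Firth fired at least as often as Wald in every scenario, with false-positive rates of about 0.05 or less.

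**Step 3: no exposed cases.** With no association, 5 exposed and 11% risk, the chance of 0 of 5 is 0.89⁵ = 0.558. Such a row is not a missed signal: with 22 cases in 200, Fisher p = 1.0. But Firth would report OR 0.70 (profile interval 0.005 to 6.5), where ordinary maximum likelihood reports nothing usable.

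**Step 4: SLS.** With one case, that patient is either exposed or unexposed, so every binary covariate has a zero cell.

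**The case against.** The SAP says only logistic regression and 95% intervals. Exact, penalised and profile-likelihood analyses all fit that wording, and a profile interval excluded 1 in every table tried in which all exposed patients were cases. This stands: the gap is silence on sparse cells, and the loss shown depends on Wald limits.

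The effects where the loss is large are extreme at low prevalence. Against 11%, a risk of 80% is an odds ratio of 4/(0.11/0.89) = 32, and 50% is about 8. At an odds ratio of 5 with 5 exposed, Wald fires 0.366 of the time, Firth 0.403 and Fisher 0.296, so little is lost. This stands for an 11% outcome. It does not hold at 37%, where 80% risk is an odds ratio of 4/(0.37/0.63) = 6.8 and Wald almost never fires.

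The analysis is exploratory, the primary prevalence objective is untouched, and the composite overlap row is less likely to have a zero cell. All true, and this limits the weight of the point.

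A reader might infer three stronger claims that the documents do not support:
- That the strongest associations in general cannot be detected. Only complete separation fails; strong associations without a zero cell usually pass at low prevalence, and many zero cells are chance results in a few exposed patients.
- That many rare subtypes are regressed. Only five outcomes are, PD is described as affecting up to 70% of patients, and SLS alone is documented as rare. The other Table 3 subgroups are only described.
- That removing SLS shows other sparse cells were left as they were. The deviations section does not say how any other sparse cell was handled, and one event is uninformative under any method.

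**Conclusion.** The point holds as a gap in the specification that has a better, cheap alternative. The SAP ties entry into the multiple model to an interval that may not exist. Under the usual Wald reading, a perfectly associated binary covariate is dropped and rows without exposed cases have no upper limit.

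The size rests on an assumed 200 patients and 3 to 8 exposed. Rarity of the individual overlap diagnoses is likewise an assumption. In the tabulated scenarios with 5 exposed and 80% risk, the Wald rule fires 33 to 44 percentage points less often than Firth. At 11% unexposed and 50% exposed risk the gap is about 6 points. Rows with adequate counts, and the prevalence results, are unaffected.

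**What to change.** Add to the logistic regression section: when any cell of the two-by-two table is zero or an expected count is below 5, the odds ratio is estimated by Firth penalised logistic regression with a profile-likelihood 95% interval; the same method is used in any multiple model containing that covariate; the reading of whether the interval excludes 1 uses these intervals; and the rows concerned are footnoted in Table 4 and Appendix 3. State the interval type for all other rows. With one event, SLS should be described only, as the deviations section in effect already does. As the SAP already carries a deviations section, a change made now should be listed there.

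The cost is one or two sentences and a different estimation command on the same data. The downside is some shrinkage in sparse rows: in the 5-of-6 example the odds ratio falls from 52 to (5.5×177.5)/(1.5×17.5) = 37, with the interval still excluding 1.

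### The SAP warns against using unadjusted 95% CIs as tests, yet uses them to call odds ratios significant and to choose variables for the multiple logistic models

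*SAP*

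**What the plan says.** Two sections of the SAP give the 95% confidence intervals a status.

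- **Section comparing PD-exposed with PD-unexposed patients (mock-up Table 2).** It states "All 95% confidence intervals (95%CI) will be two sided", then "The analyses of the secondary outcomes will be performed in sequence", then "The 95%CI will not be adjusted for multiplicity and should not be used in place of hypothesis testing".
- **Section on logistic regression (mock-up Table 4).** The scope is broad: "Independent variables, as listed in Table 4 and appendix 3, will be analysed in univariate logistic regression". The results are odds ratios "with 95% CIs excluding 1 considered indicative of potential significance". The entry rule for the next stage follows: "In multiple logistic regression analyses we plan to investigate associations that were significant by univariate analyses". The section adds that only some of these variables are expected to stay significant.

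The outcomes are "the presence of PD, airway disease, pleural disease, ILD, and SLS in a table, see table 4"; Appendix 3 uses the same five columns. The Objectives section lists these associations among the secondary objectives. The SAP names no p-value, alpha level, hypothesis test or multiplicity procedure for them.

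**The concern.** The first section asks the reader not to treat unadjusted intervals as tests. The second treats them as tests twice: once to label an association, and once to decide what enters a multiple model. Since nothing else in the SAP defines significance, the entry rule can only mean a two-sided 95% interval that excludes 1.

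At stake is how the association results are read. Across several hundred odds ratios, an unadjusted 5% screen will label some by chance. Those enter the multiple models alongside the real ones and are tested again on the same patients who selected them. Intervals from a model built in this way take no account of the selection and will tend to look more convincing than they should. A reader of the report could not tell which of the two statements governs a given odds ratio.

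**Working it through.** The SAP states no number of tests, so there is no planned figure to reproduce. The count below comes from the mock-up rows.

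**Inputs**
- Table 4: 21 single-row predictors plus 3 three-level status variables (smoking, dry cough, chest tightness), each counted once: 21 + 3 = 24. The row for overlap with other CTDs that follows the composite is taken as a header.
- Appendix 3: 2 (ethnicity, BMI) + 8 (treatment) + 1 (EULAR/ACR total) + 7 (its domains) + 5 (SLE scores) + 3 (PROMs) + 8 (plethysmography) + 4 (diffusion) + 4 (walk test) = 42.
- Listed in both: SLEDAI 2K and SLICC DI, so 2 duplicates.
- Outcomes: 5 (PD, airway, pleural, ILD, SLS).
- Cells struck out in Table 4: 4, namely the PD and pleural columns for the row beginning "Pleuritis, positive, no" and for the pleural effusion row.
- Error rate per odds ratio: 1 − 0.95 = 0.05, two-sided.

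**Planned count**
- Distinct predictors: 24 + 42 − 2 = 64.
- Odds ratios: 64 × 5 − 4 = 316.
- Expected intervals excluding 1 if no association is real: 316 × 0.05 = 15.8.

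**Count after the logged deviations**
- SLS removed (one case only): 64 × 4 − 4 = 252, and 252 × 0.05 = 12.6.
- The 7 EULAR/ACR domains also removed from Appendix 3: (64 − 7) × 4 − 4 = 224, and 224 × 0.05 = 11.2.
- The logged removal of SLICC DI from Appendix 3 changes nothing, because it was counted once.

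**Sensitivity of the planned count to the counting rule**

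| Rule | Odds ratios | × 0.05 |
|---|---|---|
| Composites only, no status variables | 61 × 5 − 4 = 301 | 15.05 |
| As above under planned count | 316 | 15.8 |
| Add the overlap row | 65 × 5 − 4 = 321 | 16.05 |
| Count duplicates twice | 66 × 5 − 4 = 326 | 16.3 |
| Two terms per status variable | 67 × 5 − 4 = 331 | 16.55 |
| Two terms, duplicates and overlap row | 70 × 5 − 4 = 346 | 17.3 |

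For overall PD alone: 64 − 2 = 62 odds ratios, and 62 × 0.05 = 3.1.

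**Why these are upper bounds.** The expected number of chance findings is 0.05 times the number of associations that are truly null, and many here are not null. The Methods place lung function and walk tests before the multidisciplinary discussion that makes the diagnosis. SLEDAI 2K and SLICC DI are listed both in full and in a version without PD, so the full scores contain PD items. Correlation among predictors leaves the expected number unchanged but makes the realised number more variable. With a single SLS case, a nominal 5% rate cannot be relied on in that column, so 224 or 252 is a safer basis than 316.

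**The case against.** Four points can fairly be made for the plan.

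1. **The caution may apply only to Table 2.** It sits under that heading, and the regression section has its own rule. A section-by-section reading is possible, so a reader who infers a flat contradiction goes further than the layout allows. But the paragraph speaks of all 95% intervals and of secondary outcomes, and the associations are a secondary objective. On the narrow reading, Table 4 would have no multiplicity statement at all. The inconsistency stands.
2. **The regression section is framed as exploratory.** It speaks of exploring and of potential significance. The next sentence drops that hedge and makes univariate significance the entry rule.
3. **Multiple regression is a second filter.** It is, and it would be wrong to say that nothing screens the univariate findings. But it reuses the same data after selection and applies no multiplicity control, so it does not bound the error.
4. **The sentence on sequence may describe only the order of reporting.** A reader might infer a gatekeeping procedure that was left unfinished. The SAP attaches no order, test or stopping rule to it and claims no error control, so that inference is not supported. The sentence is vague and needs only clarification.

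**Conclusion.** The concern holds as an inconsistency in how the unadjusted intervals are to be used, confined to one secondary objective. The interval works as a 5% test and a selection rule in one section, after another section has advised against that use.

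The size is at most about 16 chance findings expected among 316 planned odds ratios, or about 11 among the 224 left after the logged removals. These figures assume nominal coverage and that no association is real. They should not be read as a forecast of how many false findings the report contains: some predictors are linked to the outcome by construction, and the documents give no basis for estimating how many of the remainder are null. The need to reconcile the sections does not depend on which count is used. The prevalence estimate, which is the primary objective, is untouched.

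**What to change.** Reconcile the two sections as follows.

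- Delete the rule that an interval excluding 1 signals significance, and delete univariate significance as the entry rule for the multiple models.
- Report every odds ratio in Table 4 and Appendix 3 as an exploratory estimate with its unadjusted 95% interval and no significance label.
- Choose the multiple-model covariates on subject-matter grounds, for example age, sex, smoking and disease duration, and not from the univariate results. Without this step, deleting the gate would leave the models with no entry rule.
- State that the sentence on sequence refers to order of reporting only, or delete it.
- Results are already known, as the Deviations from SAP section shows. Log the change there, and describe any covariate list named now as post hoc.

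The cost is revised wording and refitting the multiple models; no new data are needed. The downside is that fewer associations can be called significant.
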